## Abstract

Regular physical activity, recommended by the WHO, is crucial in maintaining a good physical fitness level and health status and slows down the effects of aging. However, there is a lack of knowledge of whether lifelong endurance running, with a volume and frequency above the WHO limits, still brings the same benefits, or several negative effects too. The present study aims to examine the protentional benefits and risks of lifelong endurance running training in Master male athletes, as this level of physical activity is above the WHO recommendations. Within the study, four main groups of participants will be included: (1) endurance-trained master athletes, (2) endurance-trained young athletes, (3) young sedentary adults, and (4) elderly sedentary. Both groups of athletes are strictly marathon runners, who are still actively running. The broad spectrum of the diagnostic tests, from the questionnaires, physical fitness testing, and blood sampling to muscle biopsy, will be performed to obtain the possibility of complexly analyzing the effects of lifelong endurance physical activity on the human body and aging. Moreover, the study will try to discover and explain new relationships between endurance running and diagnostic parameters, not only within aging.

## 1. Introduction

Aging is a natural multisystem process affecting the individual’s body on several levels, interfering with each other. This process is characterized by progressive neural, cardiovascular, respiratory, metabolic, and skeletal muscle systems malfunctioning, manifesting as a decline of the elderly’s physical fitness and functional independence [1,2]. The relationship between human aging and their physiological function is highly individualistic and affected by inactivity [3]. On the other hand, it has been shown that reaching and maintaining a high level of both physical fitness and activity during the life span could be an effective strategy to reduce the age-related decline in physiological functions [4].

For adults (18–64) and older adults (≥65), the World Health Organization’s [5] current recommendation for physical activity for maintaining health and fitness proposes a multimodal program with 150–300 min of moderate and/or 75–150 min vigorous-intensity of endurance activity per week. Additionally, the WHO [5] also suggests increasing the time of moderate and/or vigorous activity over the recommended load for other health benefits. However, the upper limit is not given. Interestingly, there is a group of individuals, consisting of older adults, with an excessive level of physical activity and fitness, generally coined as master athletes.

Some authors suggested that master athletes represent a sample, which may be considered an “across the life span” and could be a feasible model to estimate healthy human aging [6]. In endurance sports, the physical fitness changes are evaluated mainly by cardiorespiratory fitness (CRF) testing. The CRF reflects the overall capacity of the cardiovascular and respiratory systems [7], which is measured, for instance, through maximal or peak oxygen consumption (VO_2_max). CRF could be assessed by various parameters, however, the VO_2_max is considered as a golden standard [8]. There is a linear relationship between the decline in the endurance performance and the Vo2 max in master athletes [9,10]. In addition, VO_2_max is also a predictor of cardiovascular disease and all-cause mortality [11]. The age-related decline in the VO_2_max across the lifespan is reported to be 5–10% per decade and is accelerated to more than 20% at ages over 70 years in untrained individuals [12]. In master endurance athletes, the proportion of decline can be reduced by maintaining the combination of high-intensity and volume of training up to the age of 70 years [13]. As in the general population, a significant acceleration of the decline in the VO_2_max is present in master athletes after reaching the age of 70 occurs [10]. A decrease in the CRF is caused not only by changes at the levels of the central factors such as maximal heart rate, stroke volume, and an A-V O_2_ difference which are well-documented [9], but also changes in the peripheral factors have significant effects on the decreasing CRF.

One of the well-studied and crucial peripheral factors, associated with the decline in CRF even in master athletes in their advanced age, is an age-related alteration in the skeletal muscle, which is likely a multifactorial process with a network of interacting malfunctional systems resulting in the accelerated loss of muscle mass, and a reduction in muscle strength and power [14,15,16]. This process is well known as sarcopenia. Several recent research studies showed that muscle-related alterations might be caused by factors such as central and peripheral nerve dysfunction and variations, the decrease and remodeling of motor units, fat and connective tissue infiltration, and the reduction and remodeling modifications in the cross-sectional muscle area (type II. muscle fibers reduction compared to type I. muscle fibers, and possible reinnervation) [16,17,18,19]. This multifactorial process is associated with complex structural and functional changes on the cellular level of the muscle fibers, such as a reduced satellite cells content, myonuclear number, capillarization, or mitochondrial dysfunction [16,20]. Likewise, on the subcellular and molecular levels, for example, dysfunction in EC coupling, loss and misplacement of mitochondria, and SOCE impairment have all been described within ageing. Altogether these alterations are accompanied by a development of low-grade chronic inflammation (inflammaging) [21,22].

Another factor which affects CRF is malnutrition caused by prolonged inadequate energy and/or protein intake [23,24]. In athletes, a relative energy deficiency is defined as “impaired physiological functioning caused by a relative energy deficiency and includes but is not limited to impairments of metabolic rate, menstrual function, bone health, immunity, protein synthesis, and cardiovascular health” [25]. From the aging perspective, the relative energy deficiency may negatively affect bone health and might increase the risks of osteoporosis development, which might be associated with higher risks of several fractures and injuries in the higher age of both elderly and master athletes [26,27].

The study primarily aims to investigate the benefits, and possible negative effects, of lifelong endurance training in master athletes, who actively run marathons, and compare these with elderly and young counterparts, who are less active than recommended by the WHO [5], as well as with young endurance trained athletes, who also run marathons.

Therefore, based on the evidence, the specific objectives of the study are: To examine the (a) cardiorespiratory fitness, (b) skeletal muscle structural and functional, (c) inflammatory, (d) bone health, and (e) nutritional intake parameters.To determine the effects of aging and the physical activity level on the measured parameters.To describe the relationship between the ageing and physical activity level with monitored parameters.To identify the health benefits, and possible negative effects, of lifelong one-sided endurance training.

## 2. Materials and Methods

### 2.1. Study Design

A descriptive cross-sectional study design is used among the four groups of participants. The study has been planned to be conducted from September 2021 due to gradual realization of some testing procedures.. The study protocol is designed based on SPIRIT Guidelines, and carefully described by using the SPIRIT checklist of items to be included in reports of cross-sectional studies.

### 2.2. Data Collection Scheme

Within the first hiring meeting for the study, the subjects will be fully informed about all procedures’ nature and possible risks before providing written informed consent. The familiarization, physical performance testing, and blood collection will be held at the Diagnostic Center of [name], Faculty of Physical Education and Sports, Comenius University in Bratislava, and performed by experienced examiners and healthcare professionals. DXA and muscle biopsy will be performed by certified medical professionals, surgeon at the University Hospital Ružinov, and University Hospital Antolska in Bratislava, respectively. All data will be assessed at 3 visits, and the time overview of procedures is shown in the Figure 1.

### 2.3. Sample Size

Based on the pilot study, with a mean effect size and a power of 0.9, the sample size of 14 participants per group would be needed to obtain a significant result. However, we will hire 20 subjects per group (in total, 80 subjects) to eliminate potential risks of drop out on the study outcomes. Sample size was calculated using G * Power 3.1.9.2 software.

### 2.4. Subjects

The study will involve a total of 80 healthy male subjects divided into four groups (n = 80): group 1, endurance-trained runner athletes (young athletes—YA; n = 20, age range 20–30 years); group 2, adults less active than recommended (young sedentary—YS; n = 20, age range 20–30 years), group 3, master endurance running athletes (master athletes—MA; n = 20, age range 65–75 years); group 4, seniors less active than recommended (elderly sedentary—ES; n = 20, age range 65–75 years, respectively). The groups of young and master endurance-trained runner athletes will only consist of the active marathon runners.

Subjects must meet the following inclusion criteria to participate in this study:(a)for athletes’ groups:
defined as more than 300 min per week of running activity which is, by ACSM [8], considered as vigorous intensity of endurance activity.Both groups must regularly participate in running competitions (in 10 km, half, and full marathon) for young athletes for at least 3 years and for master athletes for at least 25 years.Have a personal best on 10 km run in last season under 35 min in YA group and under 55 min in MA.(b)for groups less active than recommended: no history of regular physical activity training and no more practice than 150 min of moderate or 75 min of vigorous intensity per week.

The standard inclusion criterion for every group will be body mass index (BMI) (range 18.5–30 kg/m^2^).

Exclusion criteria will be recent or current infection, physical disabilities, malignant disease, cardiovascular, metabolic, autoimmune diseases, malnutrition, and pharmacological interference (e.g., steroids, nonsteroidal anti-inflammatory agents, immunosuppressive and antineoplastic drugs). Moreover, the use of performance-enhancing drugs in the past and during the study period is exclusionary.

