### 4.8. Data Analysis and Management

All collected data will be cleaned, coded, and entered into the computer. The anonymized data will be uploaded to a cloud server for storage. Access to this data store will be password protected. The data collected from the study will be stored on faculty One-drive cloud servers. After data collection, data from the entire study will be retrieved from the One-drive and downloaded as an Excel file (Microsoft Office, Redmond, WA, USA). Data analysis will be performed using the SPSS 23 (IBM, New York, NY, USA).

The descriptive parameters will be reported as mean values ± standard deviations (SD) and 95% of the confidence interval (95% CI). Data will be assessed for normality and homogeneity to ensure that the analysis’ assumptions will be met, using the Shapiro–Wilk test, Levene’s test, visual check of histograms, and Q–Q plots.

A one-way ANOVA with Bonferroni post hoc correction will be used to determine differences between the groups in all measured parameters. Additionally, Cohen’s d effect size (ES) will be used to calculate between-group differences and will be interpreted using the following thresholds: 0–0.2 was trivial, 0.2–0.6 small, 0.6–1.2 moderate, 1.2–2.0 large, 2.0–4.0 very large, and >4.0 extremely large effect [42].

Association analyses will be performed using the Pearson product–moment correlation coefficient. The strength of the relationship was determined using the following criteria: 0.1, small; 0.3, moderate; 0.5, large; 0.7, very large; 0.9, nearly perfect > 0.9 [43].

The results will be considered significant for values of <0.05.

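### Master athletes and elderly sedentary men share only a 65–75 age band and the planned ANOVA has no age term, so their contrast can carry an age difference of unknown size and sign

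*Protocol article*

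**What the plan says.** Section 2.4 (Subjects) of the protocol article defines the two older groups by the same age range: "master endurance running athletes (master athletes—MA; n = 20, age range 65–75 years" and "seniors less active than recommended (elderly sedentary—ES; n = 20, age range 65–75 years, respectively". It describes no matching, quota or stratum inside that range. The one inclusion criterion common to all groups is a BMI range.

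The athletes face further entry rules. Their training volume is "defined as more than 300 min per week of running activity", their competition history must run "for young athletes for at least 3 years and for master athletes for at least 25 years", and they must "Have a personal best on 10 km run in last season under 35 min in YA group and under 55 min in MA". The 55-minute limit is the same at 65 as at 75. The sedentary groups face only an activity ceiling: "no history of regular physical activity training and no more practice than 150 min of moderate or 75 min of vigorous intensity per week".

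Section 1 (Introduction) puts the fall in VO2max at 5–10% per decade, and says that it "is accelerated to more than 20% at ages over 70 years in untrained individuals". It reports an acceleration after 70 in master athletes as well, and a linear relation between the decline in endurance performance and VO2max.

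Section 4.8 (Data Analysis and Management) names the model: "A one-way ANOVA with Bonferroni post hoc correction will be used to determine differences between the groups in all measured parameters". Group is its only factor.

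**The concern.** The groups are not randomised, so the MA–ES contrast is protected from age only as far as the shared band protects it. The band is ten years wide and straddles the age at which the protocol itself places a change in slope. If the two groups differ in mean age within the band, that difference passes directly into the estimated effect of activity.

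At stake is one of the stated objectives, to determine the effects of ageing and of activity level on the measured parameters. An analysis that lets age vary freely between the two older groups cannot separate these cleanly. The exposure covers VO2peak, the primary outcome, and every age-sensitive secondary parameter, because the same model is named for all of them.

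**Working it through.** **1. Yardstick from the plan's own figure.** Section 2.3 gives 14 per group at power 0.9 but no numerical effect size, so the figure cannot be reproduced forward. Solving backwards, 14 per group implies:
- d = 1.27 for a two-sided two-group t-test at 0.05;
- d = 1.59 at the Bonferroni level 0.05/6 (four groups give 4 × 3 / 2 = 6 pairs);
- f = 0.52 for the four-group F test.

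The figure of 14 is not disputed here. It serves only to judge the size of a bias.

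**2. Age gap by chance.** Assume ages uniform on 65–75 and 20 men per group.
- SD of age = 10/√12 = 2.89 years.
- SE of the difference in mean age = 2.89 × √(2/20) = 0.91 year.
- 95% range = ±1.96 × 0.91 = ±1.8 years.

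**3. Gradient across the band.** Take the Introduction's rates: r = 5% or 10% per decade up to 70, then 20%. Two readings are assumptions: that the 20% is per decade, and that these rates apply to both groups. Relative VO2max at age a is

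V(a) = (1 − r)^((min(a, 70) − 65)/10) × 0.8^(max(a − 70, 0)/10).

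- From 65 to 70: 1 − 0.95^0.5 = 2.5%; 1 − 0.90^0.5 = 5.1%.
- From 65 to 75: 1 − (0.95 × 0.8)^0.5 = 12.8%; 1 − (0.90 × 0.8)^0.5 = 15.1%.

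**4. Shift in VO2peak for assumed age distributions.** The shift is mean V in MA divided by mean V in ES, minus 1, with ages uniform on the ranges shown. To express it in SD units, divide by an assumed coefficient of variation of 15–25%.

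| MA ages | ES ages | Gap (years) | Shift | In SD |
|---|---|---|---|---|
| 65–73 | 65–75 | 1 | 1.7–1.8% | 0.07–0.12 |
| 65–70 | 65–75 | 2.5 | 3.4–4.1% | 0.14–0.27 |
| 65–70 | 70–75 | 5 | 7.1–8.5% | 0.28–0.57 |

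The last row is complete separation of the groups, shown only as an extreme. In the first two rows the largest shift, 0.27 SD, is 0.27/1.27 = 21% of the effect implied by 14 per group. The table puts MA on the younger side for illustration; with the ages exchanged the bias would run the other way.

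**5. A secondary outcome with no activity effect.** Assume an age slope of 0.10 SD per year, 20 per group and a fixed mean-age gap. The age-driven difference is 0.10 × gap in SD units, and the two-sided two-group test then rejects as follows.

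| Gap (years) | At 0.05 | At 0.05/6 (nominal 0.8%) |
|---|---|---|
| 1 | 6% | 1% |
| 2.5 | 12% | 3% |
| 5 | 34% | 13% |

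**The case against.** **The shared band is itself a control for age.** The study is labelled descriptive and cross-sectional. This is a journal article, and the full protocol is said to be available on request, so finer matching may exist there. That much stands: the absence of matching is not proved, only that none is described. It does not rescue the analysis, because Section 4.8 is not silent. It names an unadjusted model for all parameters.

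**Chance imbalance is already in the ANOVA's error term.** This also stands. On average over samples, a chance gap does not bias the contrast. Adjustment then helps by removing the imbalance in the sample actually drawn and by reducing residual variance. Only a systematic gap biases the contrast on average.

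**A reader might infer that the eligibility rules make MA younger, so that the benefit of training is overstated.** A fixed 55-minute limit, with performance declining as VO2max does, points that way. The documents do not carry the inference through:
- No age distribution is given.
- Nothing shows that the limit binds for men who already run more than 300 minutes a week.
- The 25-year competition rule may favour older men: a man of 65 must have started by 40, a man of 75 by 50.
- The disease and drug exclusions apply to all groups and may remove older sedentary men, making ES younger.

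**A reader might also multiply the post-70 rate by a gap of 3 or 4 years and arrive at 6–8%.** Those gaps have no source in the document. Applying 2% per year to the whole gap requires both group means to lie above 70, which conflicts with the idea that MA sit low in the band.

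**Conclusion.** The point holds as a weakness in the stated analysis. The MA–ES contrast is open to a within-band age difference that the named model cannot remove, in a band where the protocol's own background expects a material gradient. A systematic gap is possible, but its size and sign cannot be derived from the document.

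For VO2peak, the plausible shift is small beside the effect the sample size implies. It would bias the estimated MA–ES difference rather than produce one. The exposure is greater for secondary parameters (bone, inflammatory, muscle) if their activity effects are modest, and for the aim of separating ageing from activity.

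These sizes rest on uniform ages, the assumed gaps, the per-decade reading of the 20% figure, the assumed coefficient of variation and the assumed age slope. The case for adjusting does not depend on which group proves older. The change should be made, but the primary comparison does not fail without it.

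**What to change.** **Change to Section 4.8.** Replace the unadjusted one-way ANOVA with an ANCOVA containing group and age. Centre age on the mean of all men in the same band, and allow separate slopes for the young and older bands. Fitting the MA–ES and YA–YS contrasts separately within each band, each with its own age term, serves equally well. Raw age across all four groups should not be used, since it is almost collinear with the young/old contrast. Report the age-adjusted contrasts alongside the unadjusted ones, and report age by group. A straight line will not follow a bend at 70 exactly, so residuals should be plotted against age in the older band.

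**Cost.** Age is needed to apply the eligibility criteria, so no new data are required. With 80 men, two slopes take the residual degrees of freedom from 80 − 4 = 76 to 74; a single-band analysis of 40 men goes from 38 to 37.

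Some precision is lost if ages differ. The variance of the MA–ES difference is multiplied by about 1 + gap²/(4 × SD²), where SD is the within-group SD of age. With an assumed SD of 2.9 years:
- 1-year gap: 1 + 1/33.6 = 1.03;
- 2.5-year gap: 1 + 6.25/33.6 = 1.19.

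This is before any gain from lower residual variance. The loss is larger if the athletes' ages are also more tightly bunched.

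**Optional.** For men still to be recruited, ES could be frequency-matched to MA on 65–69 and 70–75. This keeps 20 per group and brings the age-driven difference close to zero, but may slow ES recruitment slightly.

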## 6. Conclusions

In the present study, we will focus on revealing the positive effects and potential negative risks associated with lifelong physical activity beyond and under the recommendations defined by WHO. By using a wide range of diagnostic procedures, we gain a unique opportunity to comprehensively assess the impact of lifelong physical activity on the human body and contribute to expanding the knowledge base in the field. In addition to evaluating the current state, we assume the discovery of several relationships between diagnosed parameters, which will allow us to explain and describe the mechanisms responsible for changes occurring in the human body.

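### No group lies within the WHO activity range, and the cut-off for the less-active groups touches it, so the study cannot show whether exceeding that range adds, keeps or removes benefit

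*Protocol article*

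**What the plan says.** **The question.** The Abstract names the gap in knowledge as "whether lifelong endurance running, with a volume and frequency above the WHO limits, still brings the same benefits, or several negative effects too".

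**The reference level.** Section 1 (Introduction) gives the WHO recommendation as "150–300 min of moderate and/or 75–150 min vigorous-intensity of endurance activity per week". It adds that more activity is encouraged: "However, the upper limit is not given".

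**The primary aim.** The end of section 1 is narrower than the Abstract's question. Master marathon runners are to be compared with young and elderly men whose activity falls short of the WHO recommendation, and with young marathon runners.

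**The groups.** Section 2.4 (Subjects) sets two activity levels in each age band:
- Athletes, young (YA) and master (MA): "more than 300 min per week of running activity which is, by ACSM [8], considered as vigorous intensity of endurance activity".
- Less-active men, young (YS) and elderly (ES): "no history of regular physical activity training and no more practice than 150 min of moderate or 75 min of vigorous intensity per week". The section labels these men as below the recommended level and also as sedentary.

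**The analysis.** Section 4.8 plans a one-way ANOVA over the four groups with Bonferroni post hoc tests, and Pearson correlations.

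**The conclusion.** Section 6 says the study will address positive effects and "potential negative risks associated with lifelong physical activity beyond and under the recommendations defined by WHO".

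**The concern.** To ask whether activity above a range still brings the same benefits is to compare activity above the range with activity inside it. The plan samples both sides of the range and nothing inside it. An MA advantage over ES could come entirely from reaching the guideline at all, with nothing gained or lost beyond it. Sections 5 and 6 set the results against the WHO recommendation and offer them to coaches, clinicians and dietitians. Readers may therefore take the contrast as evidence about exceeding that level.

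The second issue is a contradiction between a label and a rule. The less-active groups are described as below the recommendation, yet their ceiling is the lowest value that meets it. Any such men would narrow the contrast that the primary aim relies on.

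**Working it through.** On this point the plan has no calculated figure to reproduce, only cut-offs, so the check sets those side by side.

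**Inputs**
- WHO range (section 1): 150–300 min moderate and/or 75–150 min vigorous per week.
- Athletes (section 2.4): more than 300 min per week of vigorous running.
- YS and ES (section 2.4): at most 150 min moderate or 75 min vigorous, and no history of regular training.
- Exchange rate (assumption): 1 vigorous minute = 2 moderate minutes. Both ends of the quoted range imply it, since 150/75 = 2 and 300/150 = 2.
- Moderate-equivalent minutes = moderate + 2 × vigorous.

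**Step 1: where the groups lie**
- WHO range: 150 to 300.
- Athletes: above 2 × 300 = 600. In vigorous minutes this is more than 300/75 = 4 times the minimum and more than 300/150 = 2 times the upper figure.
- No group is defined to lie between 150 and 300, and none between 300 and 600.

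**Step 2: can the planned contrast answer the Abstract's question?** Assume typical doses of 100 (ES), 225 (a WHO-level man) and 700 (MA) moderate-equivalent min, and an MA–ES difference of 1.0 in arbitrary units. Three dose-response curves g(t) reproduce that difference:

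| Curve | Formula | g(100) | g(225) | g(700) | MA − ES | MA − WHO level |
|---|---|---|---|---|---|---|
| Linear | (t − 100)/600 | 0 | 0.21 | 1.0 | 1.0 | +0.79 |
| Plateau | (t − 100)/125, capped at 1 | 0 | 1.0 | 1.0 | 1.0 | 0.00 |
| Inverted U | 1.6(t − 100)/125 up to t = 225, then 1.6 − 0.6(t − 225)/475 | 0 | 1.6 | 1.0 | 1.0 | −0.60 |

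The same observed contrast fits a gain, no change and a loss relative to WHO-level activity. More subjects in the same four groups would not separate the three. Pooled correlations do not help either: eligibility leaves the middle largely empty, so they would rest on two separated clusters.

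**Step 3: the less-active cut-off**

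| Moderate | Vigorous | Moderate-equivalent | Admitted by the minutes rule? | Meets the WHO minimum (150)? |
|---|---|---|---|---|
| 150 | 0 | 150 | yes, on any reading | yes |
| 0 | 75 | 150 | yes, on any reading | yes |
| 140 | 70 | 140 + 140 = 280 | yes, if the caps are separate | yes |
| 150 | 75 | 150 + 150 = 300 | yes, if the caps are separate | yes, at the top of the range |

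The ceiling is 150 if the two caps are read as equivalents and 300 if they are read separately. On either reading, the rule admits men who meet the recommendation.

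**The case against.** **The design fits the stated aim.** The four groups match the primary aim in section 1, and none of the specific objectives there asks for an above-range versus in-range comparison. The Abstract sentence describes a gap in knowledge, and section 6 already names the two sides sampled. This stands. A WHO-level arm would answer another question and is not required. What remains is that the gap sentence poses a question the study cannot answer.

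**The design is still informative about harm.** If MA were worse than ES on bone or inflammatory measures, that would show no net advantage over low activity on that measure. This also stands, although such a result could not be attributed to exceeding the WHO range.

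**The eligibility rule has two parts.** A man doing 140 moderate and 70 vigorous minutes every week would usually fail the clause on training history, and the criterion's heading steers screeners towards the intended meaning. This largely stands. Such cases are probably few, and even the 300-minute ceiling is half the athletes' floor of 600. But the clause is a separate condition. It leaves the minutes threshold inclusive and silent on combined totals.

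**A tempting rescue.** A reader might infer that regressing outcomes on weekly running volume within the 40 athletes would supply the missing evidence. It would not. All of them exceed 300 min per week, so none lies in the range. At most, such a regression is exploratory for dose above 300 min.

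**Conclusion.** The point holds on two limited counts.

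1. The Abstract's question about running above the WHO limits cannot be answered by the planned contrasts, because no group lies within 150–300 moderate-equivalent min and the athletes begin above 600. This follows from the group definitions. The three curves only illustrate it, under assumed doses and an assumed difference of 1.0.
2. The YS/ES minutes rule contradicts its label. It does so at exactly 150 moderate or 75 vigorous minutes on any reading, and up to 300 moderate-equivalent min if the caps are read separately. The combined figures rest on the 2:1 exchange implied by section 1. The protocol gives no basis for counting the men affected.

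A reader might infer that the study supports no conclusion, or that the less-active groups are heavily contaminated. The document supports neither. The aim in section 1 can be addressed as cross-sectional associations (runners versus less-active men, old versus young), and the training-history clause will keep out many men near the cut-off. The planned group comparisons and the primary outcome remain useful. What needs limiting is the claim drawn from them.

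**What to change.** 1. **Section 2.4, YS and ES.** Replace the minutes rule with strictly less than 150 moderate-equivalent min per week in total, counting vigorous minutes double. Assess it by history at screening and keep the training-history clause. The activPAL cannot screen: section 4.4 has it attached only after the fitness testing session, which yields the primary outcome. Use that week to describe the groups or for a sensitivity check on classification, not to exclude anyone.
2. **Abstract and section 6.** Restate the question and conclusion as a comparison of very-high-volume runners with below-guideline men, and of old with young. State that the results do not show whether exceeding the WHO range adds, keeps or removes benefit. Reword the reference to WHO limits as well, since section 1 says no upper limit is given.
3. **Any within-athlete analysis of running volume.** Label it exploratory for dose above 300 min per week, and do not present it as evidence on the WHO range.

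The cost is one eligibility sentence and some rewording, with no new arm. The downside is a more modest claim and possibly a few more screen failures.
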